### Randomization

Patients will be randomly assigned in a 1:1:1:1 ratio to have all their catheters cared with either 2% chlorhexidine/70% isopropyl alcohol (Chloraprep™, CareFusion™, Voisins le Bretonneux, France) or 5% povidone iodine/69% ethanol (alcohol Bétadine™, MEDA™ Pharma SAS, Paris, France) with or without prior scrubbing with an antiseptic scrub. Randomization will be stratified by hospital with the use of a web-based random-number generator producing permuted blocks to address for potential interhospital heterogeneity.

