### Cultures

Catheters will be removed aseptically and their distal 5cm will be sectioned with sterile scissors and placed in a sterile tube before being carried to the microbiology laboratory. Catheters will be cultured quantitatively by using a simplified technique of quantitative broth dilution culture [1,14].

Sets of aerobic and anaerobic blood cultures will be routinely obtained when a patient has fever, hypothermia, or other indications such as chills or sudden shock.

Skin colonization will be evaluated before catheter removal by using semi-quantitative insertion-site cultures. The insertion site will be sampled by pressing on the skin for 10 s a sterilized nutritive trypticase-soy agar plate containing antiseptic neutralizing agents (Count-tact™, 3P Pack+, Biomerieux™, Crapone, France).The plate will then be sent to the local microbiology laboratory and cultured for 48 h. The number of colony-forming units will be counted and classified as: sterile; 1 to 9 CFU; 10 to 49 CFU, 50 to 99 CFU, or ≥100 CFU per agar plate as previously done [9,15].

All cultures will be processed by the clinical microbiology laboratory according to standard methods without awareness of the randomization arm.

In cases of suspected catheter-related infection (that is, all the catheters removed with systemic inflammatory response syndrome (SIRS) or local signs of infection (pain or purulence) or positive catheter tip culture, or positive blood culture sampled 48 h before until 48 h after the catheter removal), the patient’s form will be reviewed by an independent adjudication committee. In the event of doubt, a complete blind patient record will be prepared by the clinical research associates. Two independent experts blinded to the randomization arm will classify these episodes according to infection definitions (see below). In case of disagreement, the opinion of a third expert will be sought.

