### Data collection

– For each center: number of hospital beds, type of ICU (medical, surgical or mixed, number of ICU beds, number of admissions a year in ICU, mean Simplified Acute Physiology Score II (SAPS II) [16], mean length of stay in ICU, and details of procedures for catheter insertion and maintenance.

– For each patient included: demographic data (age, sex, weight, and height), SAPS II and Sequential Organ Failure Assessment (SOFA) [1] scores at admission, length of mechanical ventilation, use of catecholamines, clinical and microbiological data needed to confirm the diagnostic of catheter-related infection.

– For each catheter: catheter insertion date, insertion site, catheter removal date, use of ultrasound guidance, insertion using guidewire exchange, experience of the operator, IGS II and SOFA scores at catheter insertion, antibiotics at catheter insertion, antibiotics used during catheter stay, administration of parenteral nutrition, propofol or blood product administration, reason(s) for catheter withdrawal, catheter tip culture result, blood culture result, local signs at catheter insertion site, status of dressing at catheter removal, evolution of signs of infection at catheter withdrawal, number and results of blood cultures drawn within 48 h around catheter removal during catheter stay, and skin colonization at removal of catheter assessed using semi-quantitative insertion site culture.

Three audits will be conducted in each center, each of them including four catheter insertions and 10 dressing changes, the first one during the first 2 months of study, the second one after inclusion of 100 patients, and the last one after inclusion of 200 patients. The costs of each antiseptic strategy will be evaluated based on material and time needed for skin preparation.

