### Assessment endpoints

Density incidence of major catheter-related infection, catheter colonization, catheter-related bloodstream infection, and skin colonization at catheter insertion site for all catheters and for arterial or central venous catheters only; mortality rate in ICU and in the hospital; length of stay in ICU and in hospital; incidence of cutaneous allergy using the International Contact Dermatitis Research Group scale [17]; cost of each strategy of skin preparation.

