### Sample size calculation

Assuming 5% of catheter-related infection rate in the 5% povidone iodine/69% ethanol group (that is, incidence density of 4 per 1,000 catheters days) and the use of at least two catheters per patient on average, 453 patients in each treatment arm will be required to demonstrate a 50% reduction of major catheter-related infection with the use of 2% chlorhexidine/70% isopropyl alcohol, with a power of 80% and a two-sided alpha risk of 5%. We plan to enroll 2,400 patients (4,800 catheters) to take into account the interaction between antiseptic efficacy and skin scrubbing and a maximum patient loss of 6%.

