### Statistical analysis

The data will be analyzed blindly with regard to treatment arms. An intention-to-treat analysis is scheduled, and it will include all patients except those with no catheter inserted and those who will have withdrawn their consent to participate in the study. No interim analyses are planned. Demographic data will be described in number and percentage or median and interquartile range for quantitative and qualitative variables and compared with χ^2^ test or Mann–Whitney, as appropriate. Kaplan-Meir curves of the risks of major-CRI and CR-BSI and catheter colonization will be plotted for each treatment group. Proportional hazard assumption will be assessed by plotting Schoenfield’s residuals with time.

Analysis of antiseptic efficacy will be carried out using a marginal Cox model stratified by centers [18]. This model takes into account the censored nature of the data and also accounts for intra-cluster (intra-patient) dependence (more than one catheter per patient) using a robust sandwich covariance matrix. The interaction between scrubbing and antiseptic effect will be sought first by forcing the interaction term in the final model. In the absence of interaction, analysis of skin scrubbing and chlorhexidine effects will be performed independently. For secondary endpoints the analyses will not be controlled for multiple testing.

Comparisons of skin cultures between groups will be assessed through multiple factor ANOVA (Center, scrubbing, antiseptic).

Analyses will be done using SAS 9.x (SAS Institute, Cary, NC,USA) and R (R foundation, Vienna, Austria) softwares.

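### The skin-culture ANOVA has no patient term, so several catheters from one patient count as independent and its standard errors are too small

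*Protocol article*

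**What the plan says.** Four sections of the protocol article bear on this.

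- **Measurement.** Under Cultures: "Skin colonization will be evaluated before catheter removal by using semi-quantitative insertion-site cultures". Colonies are counted and then put into five classes: "sterile; 1 to 9 CFU; 10 to 49 CFU, 50 to 99 CFU, or ≥100 CFU per agar plate".
- **Unit of observation.** Data collection lists, among the items for each catheter, "skin colonization at removal of catheter assessed using semi-quantitative insertion site culture".
- **Unit of randomization.** Under Randomization: "Patients will be randomly assigned in a 1:1:1:1 ratio to have all their catheters cared with either" of the two antiseptics, with or without scrubbing. All catheters of a patient therefore share one strategy. The Sample size calculation assumes "the use of at least two catheters per patient on average" and plans 2,400 patients with 4,800 catheters.
- **Analysis.** Under Statistical analysis: "Comparisons of skin cultures between groups will be assessed through multiple factor ANOVA (Center, scrubbing, antiseptic"). The same section fits a marginal Cox model to antiseptic efficacy, with a robust sandwich covariance for dependence between catheters of one patient. It says nothing comparable for the skin cultures.

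Outcomes places insertion-site colonization among the other outcomes, behind the main and second endpoints.

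**The concern.** Treatment is constant within a patient while the outcome is read on each catheter. Two plates from the same patient share skin flora, antibiotic exposure, severity and nursing care, so a positive correlation between them is to be expected. The variance of the treatment contrast then exceeds what an ANOVA on catheters reports. Center is in the model, but it does not absorb differences between patients within a center.

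At stake is an overstated claim about skin colonization. The Background treats the density of organisms at the insertion site as a major risk factor for infection, so a spurious difference here could be read as mechanistic support for an antiseptic or for scrubbing. Secondary analyses carry no multiplicity control, so nothing offsets the extra false positives.

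**Working it through.** **The plan's own figure.** The protocol gives no error rate or sample size for the skin cultures. Its only related figure is 453 patients per arm for the main endpoint. The pooled two-proportion formula with 5% against 2.5%, two-sided alpha 5% and power 80% gives

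n = [1.960 × √(2 × 0.0375 × 0.9625) + 0.842 × √(0.05 × 0.95 + 0.025 × 0.975)]² / 0.025² = 905.4, rounded up to 906 catheters per arm.

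906 / 2 = 453 patients, so the figure reproduces. It confirms that two catheters per patient is the planning value.

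**Inputs for the check**

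- Catheters per patient, m = 2 (Sample size calculation).
- Strategy constant within patient (Randomization).
- ICC: not in the protocol. Assumed 0.1 to 0.4.
- Variation in the number of catheters per patient: not in the protocol. Taken first as none, then as an assumed coefficient of variation (CV) of 0.6.

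**Formulas**

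- Design effect, equal numbers: DE = 1 + (m − 1) × ICC.
- Design effect, unequal numbers: DE = 1 + [(1 + CV²) × m − 1] × ICC. With CV 0.6 and m = 2 this is 1 + 1.72 × ICC.
- Actual type I error of a nominal 5% test that ignores clustering: 2 × P(Z > 1.96 / √DE).

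**Results**

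| Assumed ICC | DE, exactly 2 each | Type I error | 4,800 catheters are worth | DE, CV 0.6 | Type I error |
|---|---|---|---|---|---|
| 0.1 | 1.10 | 6.2% | 4,364 | 1.17 | 7.0% |
| 0.2 | 1.20 | 7.4% | 4,000 | 1.34 | 9.1% |
| 0.3 | 1.30 | 8.6% | 3,692 | – | – |
| 0.4 | 1.40 | 9.8% | 3,429 | 1.69 | 13.1% |

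**Check by simulation.** Each setting had 2,000 trials with no treatment effect, 2,400 patients and six centers. The five classes were scored 0 to 4, with assumed frequencies of 45%, 25%, 15%, 5% and 10%. The model was an additive ANOVA on center, scrubbing and antiseptic, and the test was of the antiseptic effect. The ICC was set on the latent scale; on the class scores, latent values of 0.1, 0.3 and 0.5 became 0.08, 0.24 and 0.42.

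| Latent ICC | ANOVA, exactly 2 each | ANOVA, varying, mean 2 |
|---|---|---|
| 0 | 5.2% | 4.8% |
| 0.1 | 6.6% | 5.9% |
| 0.3 | 7.3% | 9.6% |
| 0.5 | 10.0% | 11.8% |

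The Monte Carlo standard error is about 0.5 to 0.7 percentage points. At the class-score ICCs, the equal-numbers formula gives 5.9%, 7.9% and 10.1%, which agrees with the first column within that error. The same model with a patient-clustered sandwich variance gave 4.3% to 5.7% in every setting.

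The row at ICC 0 isolates the scale. With no clustering, the ANOVA on ordinal scores holds its 5% level, so the inflation comes from the clustering and not from the five classes.

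**The case against.** The strongest reply is that one sentence in a condensed article names the factors of interest and leaves variance structure to a fuller document, and that authors who handle clustering in the Cox model will not forget it here. This has some weight: nothing rules out that the full plan adds a patient effect. But the sentence is not silent on the model. It names the method and lists its factors, and the patient is not among them. The explicit correction a few lines above makes the difference between the two analyses more visible.

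The size is also open to challenge. Neither the ICC nor the CV is in the protocol, and the CV alone raises the top figure from 9.8% to 13.1%. That stands: the direction holds for any positive ICC, but the amount is a range.

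Two stronger readings are tempting, and the document supports neither.

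- A reader might infer that five unequal, open-ended classes invalidate the ANOVA test itself. The simulation at ICC 0 shows otherwise. The protocol also says that colonies are counted before they are classified, and does not say which form enters the model. What remains is interpretability: a difference in mean class score has no natural unit.
- A reader might infer that skin colonization, read from one culture before removal, cannot be a density incidence and should leave that list under Assessment endpoints. Catheter colonization is likewise read from one culture at removal. The protocol lists it the same way, and the Background reports it per 1,000 catheter-days. The reason would strike both outcomes equally and fails.

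**Conclusion.** The concern holds for clustering. Followed as written, the skin-culture ANOVA understates its standard errors for any positive correlation within patients. The true standard error is √DE times the reported one: about 5% larger at an ICC of 0.1 (√1.10 = 1.05) and about 18% larger at 0.4 (√1.40 = 1.18).

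The resulting type I error of about 6% to 10% rests on an assumed ICC and on exactly two catheters per patient. It would be about 7% to 13% at the assumed CV of 0.6. If the ICC were zero there would be no inflation.

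The consequence is limited to one of the other outcomes. The Cox analysis of major catheter-related infection already uses a patient-level robust covariance and is untouched.

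**What to change.** State that the skin-culture analysis accounts for several catheters per patient, by a patient-clustered sandwich variance, GEE with the patient as cluster, or a patient random effect. Any of these answers the clustering problem, including a clustered variance on the planned ANOVA.

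Also state which form of the culture result is analysed: count, transformed count or class. If it is the five classes, a cumulative-logit model with antiseptic, scrubbing and center, clustered on patient, is a suitable choice and gives an odds ratio with a 95% confidence interval in place of a mean score.

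The cost is a sentence or two in the analysis plan. It needs no new data and can be done in SAS or R, which the protocol already names. The cumulative-logit form has a small downside: it assumes proportional odds across the classes, which should be checked. Recruitment has started, so the change should be fixed and dated before the arms are compared.

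### The skin-culture ANOVA has no term for several catheters in one patient, although the Cox model in the same section is corrected for this, so its p-values and intervals will be somewhat too optimistic

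*Protocol article*

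**What the plan says.** All references are to the protocol article.

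- **Unit of randomization.** Randomization: "Patients will be randomly assigned in a 1:1:1:1 ratio to have all their catheters cared with either" of the two antiseptics, with or without scrubbing. Both treatment factors are therefore constant within a patient.
- **Unit of measurement.** Data collection lists, among the items for each catheter, "skin colonization at removal of catheter assessed using semi-quantitative insertion site culture".
- **Unit of comparison.** Assessment endpoints names "skin colonization at catheter insertion site for all catheters and for arterial or central venous catheters only".
- **Sites per patient.** Sample size calculation assumes "the use of at least two catheters per patient on average", with 4,800 catheters planned in 2,400 patients.
- **Scale.** Under Cultures, colonies are counted and then "classified as: sterile; 1 to 9 CFU; 10 to 49 CFU, 50 to 99 CFU, or ≥100 CFU per agar plate".
- **Skin-culture analysis.** Statistical analysis: "Comparisons of skin cultures between groups will be assessed through multiple factor ANOVA (Center, scrubbing, antiseptic").
- **Cox analysis, same section.** This model "also accounts for intra-cluster (intra-patient) dependence (more than one catheter per patient) using a robust sandwich covariance matrix".

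**The concern.** Antiseptic and scrubbing differ only between patients, while the observations are catheter sites. Two sites on one patient share that patient's flora, hygiene, antibiotics and assigned strategy, so their results are likely to be positively correlated. An ordinary ANOVA with center, scrubbing and antiseptic as its only factors uses the site-to-site residual as its error term and counts two sites on one patient as two independent pieces of information. With positive correlation, standard errors are then too small. A chance difference between antiseptics is called significant too often, and an absence of effect of scrubbing looks more precisely established than it is.

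The plan recognises this dependence for the time-to-event outcomes and corrects for it there. The sentence on skin cultures carries no such correction.

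**Working it through.** **1. The plan's own figure.** The article gives no figure for the skin-culture ANOVA. The nearest is the 453 patients per arm for the main endpoint. For 5% versus 2.5%, two-sided alpha 5% and power 80%, the usual two-proportion formula is

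n = [z(α/2)·√(2·p̄·q̄) + z(β)·√(p₁q₁ + p₂q₂)]² / (p₁ − p₂)²

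= [1.96·√0.07219 + 0.842·√0.07188]² / 0.025² ≈ 906 catheters per arm.

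Then 906 / 2 = 453 patients, an exact match. This confirms that the plan works with m = 2 catheters per patient.

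**2. Inputs for the ANOVA.** From the document: m = 2 and 4,800 sites. Assumed, because the document does not give it: an ICC of the skin-culture response between sites of one patient of 0.05 to 0.50. Also assumed, for the unequal case: a coefficient of variation (CV) of 0.5 in the number of catheters per patient.

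**3. Formulas.**

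- Design effect, equal numbers: DE = 1 + (m − 1)·ICC = 1 + ICC.
- Design effect, unequal numbers: DE = 1 + [(1 + CV²)·m − 1]·ICC = 1 + 1.5·ICC at CV 0.5.
- True two-sided error of an unclustered test at nominal 5%: 2·[1 − Φ(1.96/√DE)].
- Width of the correct interval relative to the reported one: √DE.
- Effective number of sites: 4,800/DE.

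Example, ICC 0.20 and two catheters each: DE = 1.20, √DE = 1.095, 1.96/1.095 = 1.79, true error 7.4%.

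| ICC (assumed) | DE, 2 each | True error | Width ratio | Effective sites | True error, CV 0.5 | Width ratio, CV 0.5 |
|---|---|---|---|---|---|---|
| 0.05 | 1.05 | 5.6% | 1.02 | 4,571 | 5.9% | 1.04 |
| 0.10 | 1.10 | 6.2% | 1.05 | 4,364 | 6.8% | 1.07 |
| 0.20 | 1.20 | 7.4% | 1.10 | 4,000 | 8.6% | 1.14 |
| 0.30 | 1.30 | 8.6% | 1.14 | 3,692 | 10.4% | 1.20 |
| 0.50 | 1.50 | 11.0% | 1.22 | 3,200 | 13.8% | 1.32 |

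**4. Simulation check.** Settings: 2,400 patients, six centers, the 2×2 factorial, no true effect, and five ordered classes scored 0 to 4. The class distribution was flat, skewed or very skewed. The number of catheters was either two each or variable with mean 2. Each setting had 1,500 runs, so the Monte Carlo standard error near 5% is √(0.05·0.95/1,500) ≈ 0.6 points. Here the correlation is set on the latent scale behind the classes, so the results need not equal the table.

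| Latent correlation | ANOVA as written | With patient-clustered variance |
|---|---|---|
| 0 | 4.3% to 5.6% | 4.3% to 5.6% |
| 0.2 | 6.9% to 8.7% | 4.6% to 6.3% |
| 0.5 | 8.9% to 13.3% | 4.6% to 5.5% |

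The first row isolates the effect of scoring ordered classes: the error rate stays nominal within simulation error. The other rows show that the inflation comes from clustering, and that a patient-clustered variance removes it, apart from simulation error.

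**The case against.** The article is a condensed account, and a full analysis plan may exist. The parenthesis lists factors and does not describe the error structure, so independence of sites is a reading of the text, not a statement in it. The authors plainly know about the dependence, because they handle it for the Cox model. Skin colonization stands among the other outcomes, and secondary analyses are not controlled for multiple testing, so these p-values never carried a strict 5% guarantee. At a low correlation the inflation is trivial.

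Most of this limits the weight of the point rather than removing it. The article does not leave the method open: it names the model and lists its factors, and it states the correction for one analysis and not for the other. Someone who follows the text literally obtains the understated variance. The absence of a multiplicity adjustment does not excuse an individual test whose own error rate is off.

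Two stronger inferences should be resisted.

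- A reader might conclude that analysing five unequal classes with an open top class also makes the p-values too small. The check at zero correlation shows that it does not. Scoring the classes only makes a mean score hard to interpret.
- A reader might conclude that class codes are the response and that no mean count can be formed. The article does not say so: colonies are counted before they are classified, and the ANOVA response is not named.

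**Conclusion.** The point holds as a modest one. As written, the skin-culture ANOVA ignores the within-patient dependence that the same section corrects for in the Cox model. For an assumed ICC of 0.05 to 0.50 with two catheters per patient, the true type I error is about 5.6% to 11% instead of 5%, and correct intervals are about 1.02 to 1.22 times as wide as those reported. With unequal numbers of catheters (CV 0.5) the upper ends are 13.8% and 1.32. At an ICC of 0.05 to 0.10 the effect is small.

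This rests on three assumptions: a positive within-patient correlation, whose size the document does not give; an analysis that pools all catheters; and an ANOVA run with only the listed factors. Analyses restricted to one catheter type would have fewer sites per patient and so less inflation.

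A reader might infer that the trial's main claims are at risk, or that skin cultures are their formal support. The Outcomes section does not bear this out. The main endpoint is major catheter-related infection, the second is catheter colonization, and skin colonization is one of the other outcomes.

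**What to change.** Keep center, scrubbing and antiseptic as factors, and add two statements to the sentence on skin cultures:

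1. **Variance.** Standard errors are clustered on the patient with a robust variance, as already planned for the Cox model, or the model has a patient random effect.
2. **Response.** Say whether the count, a transformation of it, or the five-class result is analysed. If it is the five classes, a proportional-odds model with the same three factors and the same clustering is an option, reported as a common odds ratio with 95% CI. It brings its own proportionality assumption and is not needed to correct the error rate.

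The cost is a sentence or two of wording and standard procedures in SAS or R. No new data are needed. The downside is slightly wider intervals for skin cultures.

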### Length of patient follow-up

Patients will be followed up for the duration of their stay in ICU. Insofar as possible the catheter will be removed before patients’ discharge from ICU. If not, one peripheral and one through-the-line blood culture will be drawn at discharge and a visit at day 3 will take place in order to enquire about the diagnostic of catheter-related infection.

